### Sample size and Analysis

Local pilot data suggested that 40% of people would receive appropriate osteoporosis medications at 6 months. Similarly, it was anticipated that 40% of people would receive appropriate falls assessment at 6 months. We determined a minimal clinically important difference of 20% and with a two-tailed alpha of 0.05, power of 0.80, the patient as the unit of allocation and analysis, and assuming a loss to follow-up of 10%, a total sample size of 200 patients was needed.

Descriptive statistics will be calculated for all variables of interest. Continuous measures will be summarized using means and standard deviations and categorical measures will be summarized using percentages. The principal outcome measure will be assessed using a two sample two-sided test of proportions and will be performed on an intention to treat basis.

Ethics approval was received from the Joint Group Health Centre/Sault Area Hospital Research and Ethics Board. This trial has been registered with clinicaltrials.gov (ID: NCT00465387)

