### Allocation and Blinding

Eligible patients were randomized using a computer generated randomization scheme under supervision of the study biostatistician, into an immediate intervention protocol (IP) group or to a delayed intervention protocol (DP) group. All members of the DP group received usual health care during the first 6 months of the main study and then were able to receive the intervention after this period. Patients, physicians and outcomes assessors could not be blinded to the fact that patients were part of a falls and fracture prevention study. All patients were followed-up at 6 and 12 months after the completion of the initial assessment.

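### On the most natural reading (40% v 60%), 200 patients with 10% loss give about 77% power, not 80%, and the arm that the 40% belongs to is not stated

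*Protocol article*

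**What the plan says.** All the planning figures stand in the Protocol article under Sample size and Analysis.

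- Osteoporosis outcome: "Local pilot data suggested that 40% of people would receive appropriate osteoporosis medications at 6 months".
- Falls outcome: "it was anticipated that 40% of people would receive appropriate falls assessment at 6 months".
- Effect: "We determined a minimal clinically important difference of 20" per cent.
- Error rates: "with a two-tailed alpha of 0.05, power of 0.80".
- Unit: "the patient as the unit of allocation and analysis".
- Conclusion: "assuming a loss to follow-up of 10%, a total sample size of 200 patients was needed".
- Test: "The principal outcome measure will be assessed using a two sample two-sided test of proportions".

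Under Allocation and Blinding, patients are randomised "into an immediate intervention protocol (IP) group or to a delayed intervention protocol (DP) group"; no ratio is given. The article does not attach the 40% to an arm, does not write out the rate in the other arm, does not say whether the 20% is absolute or relative, and does not name the sample-size formula.

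**The concern.** A pilot rate followed by a minimal important difference normally means a control rate plus an increment, here 40% rising to 60%. On that reading the stated total is too small for the stated power once the stated loss is taken off. This sentence is the only justification of size for both primary outcomes, so any shortfall applies to each. A reader faced with a null result would credit the trial with 80% power that its own inputs do not provide. This is not a matter of an article leaving detail to a fuller document: inputs and result are both printed, and on this reading they disagree.

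**Working it through.** **Inputs.** From Sample size and Analysis: 40%, a difference of 20, two-sided alpha 0.05 (z = 1.96), power 0.80 (z = 0.8416), 10% loss, patient as unit, so no design effect. Assumed: the 40% is the usual-care rate, the 20 is absolute, and allocation is 1:1 (unequal allocation would need more patients). A relative 20% (40% v 48%) can be set aside: (1.96 + 0.8416)² × (0.24 + 0.2496) / 0.08² is about 600 per arm, nowhere near 200.

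**Step 1. Evaluable patients for 40% v 60%.**

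- Pooled variance: n = [1.96 × √(2 × 0.5 × 0.5) + 0.8416 × √(0.24 + 0.24)]² / 0.20² = 96.9, so 97 per arm, 194 in total.
- Unpooled variance: n = (1.96 + 0.8416)² × (0.24 + 0.24) / 0.20² = 94.2, so 95 per arm, 190 in total.
- Arcsine: 97 per arm, 194 in total.
- Pooled with continuity correction: n′ = (n/4) × [1 + √(1 + 4/(n × 0.20))]² with n = 96.9 gives 106.7, so 107 per arm, 214 in total.

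**Step 2. Try to reach 200 with 10% loss.**

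| Formula, 40% v 60% | Evaluable total | Randomised, n / 0.9 | Randomised, n × 1.1 |
|---|---|---|---|
| Unpooled | 190 | 212 | 210 |
| Pooled or arcsine | 194 | 216 | 214 |
| Continuity-corrected | 214 | 238 | 236 |

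(Rounded up per arm.) None gives 200. One-sided testing does not either: 154 evaluable, 170 to 172 with loss.

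**Step 3. What loss would 200 cover?** 1 − 194/200 = 3% (pooled); 1 − 190/200 = 5% (unpooled).

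**Step 4. Power with 200 randomised and 10% lost: 180 evaluable, 90 per arm.**

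- Pooled: z = [0.20 − 1.96 × √(2 × 0.25/90)] / √(0.48/90) = (0.20 − 0.1461)/0.0730 = 0.738, power 77.0%.
- Unpooled: z = 0.20/0.0730 − 1.96 = 0.779, power 78.2%.
- Arcsine: 77.1%.
- Exact binomial enumeration of the pooled z test: 75.6%.
- With a continuity-corrected test, which the article does not mention: 72.1%.

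With nobody lost (100 per arm), the pooled formula gives 81.2%. At 90 per arm, the difference detectable with 80% power above a 40% control rate is 20.4 points (unpooled) to 20.7 points (pooled).

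**Step 5. The other reading: 40% under intervention, 20% under usual care.**

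- Pooled: [1.96 × √(2 × 0.3 × 0.7) + 0.8416 × √(0.16 + 0.24)]² / 0.20² = 81.2, so 82 per arm; 82/0.9 rounds up to 92 per arm, 184 randomised.
- Continuity-corrected: 90.9, so 91 per arm, 182 evaluable. Then 182 × 1.10 = 200.2, or 91/0.9 rounded up to 102 per arm, 204 randomised.
- Power at 90 per arm: 83.9% (pooled).

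So one standard formula, with the loss included, does reproduce 200 on this reading.

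**The case against.** The strongest objection is that 40% v 60% is inferred, and Step 5 shows a reading under which 200 is right. The document offers that reading some support. Setting and Study Population excludes patients already on appropriate osteoporosis therapy, which makes 40% appropriately treated within six months of usual care look high, and the Background describes these interventions as little used.

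The text still leans the other way. No 20% rate appears anywhere. A pilot figure followed by a minimal important difference is the usual form of baseline plus increment. The same 40% is also given for receiving a falls assessment, although the section on falls assessment and management has a research nurse assess participants at home, so 40% would be a strangely low rate under intervention. The objection does not remove the mismatch, but it makes the conclusion conditional.

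Two stronger conclusions are tempting, and the document supports neither:

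- Because 194 is close to 200, a reader might infer that the 10% allowance was simply left out. The article shows no working, and under Step 5 the allowance was applied. All that can be said is that 200 does not reproduce for 40% v 60%.
- Because the analysis is by intention to treat, a reader might count the lost 10% as failures (0.9 × 40% = 36% v 0.9 × 60% = 54%, 100 per arm) and quote about 73% power. The article states no such rule, so that figure is hypothetical.

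It can also be said that the effect is small, and that outcomes come mainly from chart review of the electronic record, so patients who drop out of contact may still be assessable. Both points are fair and bear on severity. Neither repairs the printed calculation, which itself assumes 10% loss.

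**Conclusion.** The point holds in conditional form. If 40% is the usual-care rate, the 20% is absolute and allocation is 1:1, then 200 randomised with 10% loss gives about 76% to 78% power for each primary outcome rather than 80%, and about 210 to 216 would have been needed without a continuity correction. The shortfall is some 10 to 16 patients, 2 to 4 points of power, or less than one percentage point in the detectable difference. If 40% is instead the intervention rate against 20%, the stated size is adequate and the only defect is that the sentence does not say so. Either way the sentence needs correcting, because the arm, and hence the power, cannot be read from it. Severity is moderate to minor: the primary test, the estimate and the type I error are untouched.

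**What to change.** In Sample size and Analysis, state the expected rate in each arm for each primary outcome, say that the 20% is in absolute percentage points, and name the formula, the allocation ratio and how the 10% loss was applied. Only the investigators can confirm which arm the 40% describes.

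- If it is usual care, replace the conclusion with: *200 randomised, 180 evaluable after 10% loss, gives about 77% power to detect 40% v 60% (two-sided alpha 0.05).*
- If it is the intervention arm, write out 20% v 40% and the continuity-corrected formula, and keep 200.

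The cost is a sentence or two and, in the first case, a stated power about 3 points lower. The Methods section dates the trial to March 2003 to January 2006, so enrolment cannot change, and no extra patients are called for.

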### Setting and Study Population

This study was completed in the Algoma District of Ontario, Canada, a geographically vast area with Sault Ste Marie (population 78 000) as its main city. The study represented a partnership among consumers, providers and other stakeholders interested in reducing falls and fractures in the community. It was conducted by the Group Health Centre (GHC), a multidisciplinary, multi-specialty, not-for-profit health service community centre, in partnership with Sault Area Hospital (SAH), a facility with 250 active beds. When the study was initiated, the Group Health Centre had 44 000 registered patients. Distinguishing features of the GHC are multiple types of health care professionals integrated within a health care delivery system, capitation funding and an electronic medical record system (EMR). The study was also completed in partnership with the Algoma Community Care Access Centre; the Algoma Health Unit; and the Slips, Trips and Falls Committee of Sault Ste Marie Safe Communities Partnership, a community-based falls prevention coalition.

Patients were eligible for inclusion in the study if they were community-dwelling, aged 55 years or older, able to give informed consent, and were identified to be at risk for a future fracture according to one of the following criteria:

1. attended the hospital Fracture Clinic for a non-pathological fracture of the vertebrae, hip or wrist or BMD in the past year with a T-score of ≤ -2.0;

2. attended the hospital Emergency Department with a fall and found to be at high risk for falls as defined by a Timed Up and Go[32] result of greater than 14 seconds; or,

3. were self-referred or referred by a health care provider because of perceived high risk of fracture, and identified as a high risk for falls defined by a Timed Up and Go result of greater than 14 seconds.

Patients were excluded if they were already receiving appropriate therapy for osteoporosis as outlined in the Osteoporosis Canada guidelines. [23]

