## Discussion

It is critical that the health care community address the deficiencies that exist with respect to knowledge translation and management of osteoporosis given the significant burden of disease associated with falls and fractures. Implementing evidence-based strategies with timely follow-up and treatment is especially important in acute-care settings (e.g. fracture clinics and hospitals), since the individuals who present in these settings are often at highest risk for future sequelae. [39,40] The study will be able to evaluate the clinical and cost impact of a multidisciplinary intervention program for falls risk and osteoporosis management on appropriate assessment and treatment compared to usual care in a northern community. Its design is pragmatic and is focused on ensuring that a local program is evaluated before a decision is made to implement it long-term. The combination of clinical and cost evidence generated is essential information for health care decision makers assessing the long term viability of the program.

Limitations of this trial include that randomization will occur at the level of the patient rather than at the practice level and a short follow up time of 6 to 12 months. Because of the small number of primary care practices in this location, we are unable to randomize at the practice level. Given that that it is extremely difficult to change behaviour[41], and that there are significant time constraints to the primary care visits in this region due to physician shortages, we anticipate that this will not have a significant impact on the study outcomes.

The findings from this trial will provide information of interest to many stakeholders including patients, health care managers, public health officials, policy makers, and health care professionals amongst others. To our knowledge, it represents the first Canadian trial attempting to bridge the evidence-to-practice gap around osteoporosis and falls prevention. Moreover, it includes a successful partnership amongst relevant community stakeholder groups which is required to ensure appropriate implementation of a multi-faceted intervention and to facilitate sustainability of effective interventions.

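### The primary test of proportions is valid but unadjusted, and gives up a modest, unquantified amount of precision available from entry route and age

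*Protocol article*

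**What the plan says.** Under Sample size and Analysis, the protocol article states: "The principal outcome measure will be assessed using a two sample two-sided test of proportions", by intention to treat. No covariate is named. The article has two primary outcomes, one for osteoporosis management and one for falls assessment.

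The same section gives the design figures: "with a two-tailed alpha of 0.05, power of 0.80", a "minimal clinically important difference of 20" per cent, "assuming a loss to follow-up of 10" per cent, and a total of 200 patients. The anticipated rates are "Local pilot data suggested that 40% of people would receive appropriate osteoporosis medications at 6 months" and "it was anticipated that 40% of people would receive appropriate falls assessment at 6 months". Neither sentence says which arm the 40% describes.

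Setting and Study Population requires age 55 or over and lists three entry routes:
- a fracture clinic visit or a low bone density result;
- an emergency visit for a fall with a slow Timed Up and Go;
- patients who "were self-referred or referred by a health care provider because of perceived high risk of fracture", again with a slow Timed Up and Go.

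Allocation and Blinding describes a computer-generated scheme and mentions no stratification. On practices, the Discussion says: "Because of the small number of primary care practices in this location, we are unable to randomize at the practice level".

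**The concern.** The entry routes differ on features close to the two primary outcomes. The first route rests on a fracture or low bone density and sets no mobility threshold. The other two rest on a slow Timed Up and Go and set no bone criterion. It is reasonable to expect the chance of appropriate osteoporosis management, or of a falls assessment, to differ between them. If it does, a chance imbalance in route passes into the raw difference in proportions, and the unadjusted standard error is larger than it need be.

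Adjusting for variables fixed before randomisation and then averaging the predicted risks over the trial population targets the same risk difference. The choice is therefore between two estimators of one quantity, and the more precise one uses information already in hand.

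**Working it through.** **Inputs.** From Sample size and Analysis: two-sided α = 0.05, power 0.80, a difference of 20 points, a rate of 40% in an unnamed arm, 10% loss, N = 200. Assumed: 1:1 allocation, hence 200 × 0.9 / 2 = 90 evaluable per arm. R², the share of within-arm outcome variance explained by the covariates, is also assumed, because the article gives no value.

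**Step 1. The plan's own figure.** With p̄ the mean of the two rates and d their difference:

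n per arm = [1.96·√(2p̄(1−p̄)) + 0.8416·√(p₁(1−p₁)+p₂(1−p₂))]² / d²

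- 40% v 60%: (1.96·√0.50 + 0.8416·√0.48)² / 0.04 = 96.9, so 97 per arm, 194 in total, and 194/0.9 = 216 after loss.
- 20% v 40%: (1.96·√0.42 + 0.8416·√0.40)² / 0.04 = 81.2, so 82 per arm, 164 in total, and 183 after loss. With a continuity correction, 182 becomes 203.

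The stated 200 is not reproduced for 40% v 60% once the loss is included; 194 without it is close. For 20% v 40% with continuity correction, 203 is close to 200.

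**Step 2. Power of the stated test at 90 per arm.** Power = Φ{(d√n − 1.96·√(2p̄(1−p̄))) / √(p₁(1−p₁)+p₂(1−p₂))}

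- 40% v 60%: Φ{(1.897 − 1.386)/0.693} = Φ(0.738) = 77.0%.
- 20% v 40%: Φ{(1.897 − 1.270)/0.632} = Φ(0.992) = 83.9% (79.5% with continuity correction).

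**Step 3. Effect of adjustment.** Adjustment acts like an increase in sample size to n/(1−R²) per arm. The CI half-width for 40% v 60% is 1.96·√(0.48/90)·√(1−R²).

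| Assumed R² | Effective n per arm | Power, 40% v 60% | N needed with 10% loss, 40% v 60% | CI half-width (points), 40% v 60% | Power, 20% v 40% |
|---|---|---|---|---|---|
| 0 | 90.0 | 77.0% | 216 | 14.3 | 83.9% |
| 0.02 | 91.8 | 77.8% | 212 | 14.2 | 84.7% |
| 0.05 | 94.7 | 79.1% | 205 | 13.9 | 85.8% |
| 0.10 | 100.0 | 81.2% | 194 | 13.6 | 87.6% |
| 0.15 | 105.9 | 83.4% | 184 | 13.2 | 89.4% |

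For 40% v 60%, 80% power is reached at R² = 1 − 90/96.9 ≈ 0.07.

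**Step 4. Simulation check.** This used 20,000 trials at 90 per arm, 40% v 60%, comparing the pooled z-test with a covariate-adjusted linear model using HC3 standard errors. Unadjusted power was about 75%. Adjusted power was 76.7%, 78.5%, 80.1% and 82.9% at R² of 0.02, 0.05, 0.10 and 0.17. The pattern is the same at a slightly lower level, and here it takes R² of about 0.10 to reach 80%.

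**Step 5. What such R² values imply.** Suppose half the patients enter by the first route and the overall rate is 40%. Then R² = 0.25 × gap² / 0.24, where gap is the difference in outcome rate between that route and the others. A 20-point gap gives about 0.04 and a 30-point gap about 0.09. Conversely, R² of 0.05, 0.10 and 0.15 needs gaps of about 22, 31 and 38 points from route alone. The between-arm difference in route share has SD √(2 × 0.25/90) = 7.5 points. Under a 30-point gap, a 1-SD imbalance therefore moves the estimate by about 2 points, and a 2-SD imbalance by about 4.5.

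**The case against.** The strongest reply is that nothing here is wrong. Patients are randomised individually, no stratification is described, and the test matches that design: it is unbiased over repeated randomisations, and its type I error rate already allows for chance imbalance. That stands. A reader might infer that the test is invalid or biased, and the article does not support this.

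A reader might also infer that the trial is short of its stated power and that adjustment rescues it. That is conditional. The shortfall exists if 40% is the usual-care rate. Pilot data make this the natural reading, but the article does not say so, and under 20% v 40% there is none unless a continuity correction is applied.

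The prognostic value of the covariates is an expectation. The article reports no association between route or age and either outcome. Two of the three routes share one mobility threshold, and excluding patients already on appropriate osteoporosis therapy may narrow the spread. The gaps in Step 5 are large beside a target effect of 20 points. All this limits the size of the gain. It does not remove the case for adjusting.

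Modelling the physician is not free. Practices are few, and Interventions notes that some patients have no primary care physician. A random intercept or clustered variance could be unreliable, so it does not belong in the primary model.

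On timing, Methods places the trial between March 2003 and January 2006, so a change of primary analysis is late. The analyses are nevertheless written in the future tense, so the change remains open provided that outcomes by arm have not been examined.

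**Conclusion.** The point holds as a modest efficiency matter. The article fixes a valid unadjusted test and so forgoes precision from entry route and age, both known at entry, with no stratification described. If 40% is the usual-care rate, the gain over 77.0% power is about 1 point at R² = 0.02, 2 at 0.05, 4 at 0.10 and 6 at 0.15. If 40% is the intervention rate, power starts at about 84% and the benefit is a narrower interval only. These figures rest on 1:1 allocation, 90 evaluable per arm and an assumed R². An SAP that is not shown might add a supportive adjusted analysis, but the principal test stated in the article would still be the unadjusted one.

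**What to change.** Before outcomes by arm are examined, specify the following for each of the two primary outcomes:

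- **Primary:** a marginal risk difference with 95% CI, standardised from a logistic model with treatment, entry route and age, and with sex if it was recorded. The article does not list sex as a baseline variable; it mentions men and women only in the Economics substudy.
- **Supportive:** the two-sample test of proportions as now stated.
- **Sensitivity only:** any model that includes the physician, with a stated rule for patients who have none.

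State also which arm the 40% refers to, so that the power position is clear.

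The cost is slightly more analysis work, plus a dated record that the change preceded unblinded analysis. If outcomes by arm have already been seen, keep the stated test as primary and report the adjusted risk difference as supportive.

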## Discussion

It is critical that the health care community address the deficiencies that exist with respect to knowledge translation and management of osteoporosis given the significant burden of disease associated with falls and fractures. Implementing evidence-based strategies with timely follow-up and treatment is especially important in acute-care settings (e.g. fracture clinics and hospitals), since the individuals who present in these settings are often at highest risk for future sequelae. [39,40] The study will be able to evaluate the clinical and cost impact of a multidisciplinary intervention program for falls risk and osteoporosis management on appropriate assessment and treatment compared to usual care in a northern community. Its design is pragmatic and is focused on ensuring that a local program is evaluated before a decision is made to implement it long-term. The combination of clinical and cost evidence generated is essential information for health care decision makers assessing the long term viability of the program.

Limitations of this trial include that randomization will occur at the level of the patient rather than at the practice level and a short follow up time of 6 to 12 months. Because of the small number of primary care practices in this location, we are unable to randomize at the practice level. Given that that it is extremely difficult to change behaviour[41], and that there are significant time constraints to the primary care visits in this region due to physician shortages, we anticipate that this will not have a significant impact on the study outcomes.

The findings from this trial will provide information of interest to many stakeholders including patients, health care managers, public health officials, policy makers, and health care professionals amongst others. To our knowledge, it represents the first Canadian trial attempting to bridge the evidence-to-practice gap around osteoporosis and falls prevention. Moreover, it includes a successful partnership amongst relevant community stakeholder groups which is required to ensure appropriate implementation of a multi-faceted intervention and to facilitate sustainability of effective interventions.

